## Abstract

**Background:**

Symptoms of mental illness are often triggered by stress, and individuals with mental illness are sensitive to these effects. The development of mobile health (mHealth) devices allows continuous recording of biometrics associated with activity, sleep, and arousal. Deviations in these measures could indicate a stressed state requiring early intervention. This paper describes a protocol for integrating an mHealth device into a community mental health team to enhance management of severe mental illness in young adults.

**Objective:**

The aim of this study is to examine (1) whether an mHealth device integrated into a community mental health team can improve outcomes for young adults with severe mental illness and (2) whether the device detects periods of mental health versus deterioration.

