### Aims and Hypotheses

The aims of this study are to (1) examine whether case management augmented by an mHealth device integrated into a youth mental health team can improve treatment outcomes for young people with a severe mental illness and (2) examine whether the mHealth device can predict mental deterioration versus health for those allocated to the integrated arm of the trial. We hypothesize that (1) case management for a severe mental illness enhanced by an mHealth device integrated into a youth mental health team will result in better outcomes than case management with an unintegrated device and (2) physiological data from an mHealth device will identify periods of mental deterioration.

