### Measurements

#### Overview

The primary outcome for the RCT is the extent to which the integrated mHealth device can prevent mental deterioration. The within-subjects components of the trial will examine if differences in activity, sleep, and EDA predict mental deterioration versus stability. A variety of measurements will be taken, including self-report, case manager report, biometric measures from the Embrace2, EMAs of stress, chart reviews, as well as qualitative reports from case managers and participants regarding the acceptability of the device. Multimedia Appendix 1 shows a summary of the measurements taken at each time point.

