#### Assessments of Mental Deterioration

Case managers and blinded clinical staff will make monthly assessments of participants using the Clinical Global Impression Scale (CGI) [26], the Social and Occupational Functioning Assessment Scale (SOFAS) [6], and chart reviews.

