### Power Calculations and Statistical Analysis

The primary outcome for this study is to compare changes in treatment-related outcomes before and after the intervention for participants enrolled in the integrated versus unintegrated conditions. There are currently no trials examining the augmentation of treatment with an mHealth device, so sample size estimations are made using general calculations. Assuming a moderately sized advantage of the integrated (ie, unWIRED) versus unintegrated device on outcomes (effect size=0.5, 80% power, and a 2-tailed α of .05), we will require 63 participants per group.

The RCT component generally compares measures of mental health, distress, and functioning between the conditions, adjusted for baseline scores. For example, this analysis may focus on an intent to treat using a hierarchical linear model (HLM) to test the differential effects of the two treatment conditions, because this method allows the number of observations to vary between participants and handles missing data by calculating estimates of trajectories using maximum likelihood estimation. Fixed effects could be tested for intervention condition and time of assessment. Random effects in the unstructured models provide an index of the relative effects of the treatments over time. Fixed effects parameters may be tested with the Wald test (*t* test, *P*<.05, 2-sided) and 95% confidence intervals. Analyses will focus on the primary outcomes (ie, CGI scores) and secondary outcomes (eg, APQ6, BASIS-24, DASS-21, PSQI, and AQoL-8D) between the unWIRED group and the active control group, with the main outcome points being at the 6-month follow-up relative to baseline. All results are based on estimated mean values derived from HLM analyses. The within-subjects analysis will be comprised of linear fixed effects models using physiological measurements (ie, sleep, activity, and EDA) to predict measures of mental health, distress, and functioning. Baseline variables may be used as covariates when analyzing individual and between-group differences (eg, age, illness severity, treatments, and personality differences). Thematic analysis [38] will be used to examine individual and group qualitative feedback regarding the acceptability of the mHealth device and the unWIRED intervention for participants and case managers; there will be approximately 10-20 participants in the patient and clinician groups.

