## Discussion

This study will determine whether integrating an mHealth device into clinical care is useful and effective in managing severe mental illness in young adults in the community. We plan to test this approach in a frontline community mental health setting, where we can examine its feasibility, acceptability, and efficacy for patients and case managers. While previous studies use mHealth devices for participants to self-monitor, this is among the first to stream information to both a patient and the treating mental health team. We hypothesize that the device will identify periods of increased stress and risk of mental deterioration.

A strength of this design is that it examines both between- and within-subjects components. An RCT is a gold standard in determining treatment efficacy, and the within-subjects design can control for individual differences. This study also takes several types of measurements regarding evidence of mental deterioration, symptoms, and functioning. Potential limitations with this protocol should also be noted. This study intends on using participants with a variety of diagnoses, with varying severities, and with psychosocial difficulties. While this increases its ecological validity, the variation may make it more difficult to detect group differences. This limitation highlights the importance of controlling for relevant variables as well as studying within-subjects variation. Furthermore, even severely unwell patients are more often stable than deteriorating, providing fewer opportunities to test the efficacy of the unWIRED approach. Hence, examining process variables is important, as is the mixed methods approach employed in this study. Finally, the design incorporates several measures to detect an effect; however, this increases the likelihood of type I error.

While ambitious, this project’s clinical implications are potentially significant. Any treatment that improves collaboration and early intervention may have a far-reaching impact on the treatment of severe mental illness in the community. The intervention could allow clinicians to remotely and unobtrusively monitor severely unwell patients in the community and provide an effective means to augment treatment.

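### Aim 2 asks whether the device tells deterioration from health, but the only stated analysis is a linear model of scores, which tests association and does not measure discrimination

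*Protocol article*

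**What the plan says.** The protocol article words the second aim as a contrast between two states each time it appears.

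- Abstract, Objective: "whether the device detects periods of mental health versus deterioration". The abstract's Methods repeat the question.
- Aims and Hypotheses, Aim 2: to "examine whether the mHealth device can predict mental deterioration versus health for those allocated to the integrated arm of the trial".
- Aims and Hypotheses, Hypothesis 2: "physiological data from an mHealth device will identify periods of mental deterioration".
- Measurements, Overview: the within-subjects part will "examine if differences in activity, sleep, and EDA predict mental deterioration versus stability".

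The analysis is given in one sentence under Power Calculations and Statistical Analysis: "The within-subjects analysis will be comprised of linear fixed effects models using physiological measurements" (sleep, activity and EDA) "to predict measures of mental health, distress, and functioning". The outcomes are scores. The article defines no deteriorated period and names no measure of discrimination. Chart reviews will collect signs of relapse and hospitalizations, but no stated analysis links these to the device signals.

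The Discussion adds that "even severely unwell patients are more often stable than deteriorating, providing fewer opportunities to test the efficacy of the unWIRED approach". It makes this remark about the efficacy of the intervention, not about the detection aim.

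**The concern.** Detection and association are different estimands. A slope estimates how far a score moves, on average, per unit of a physiological signal. Detection concerns how many deteriorated periods are flagged and how many stable periods are flagged wrongly. With several hundred participant-months, a weak association can reach P<.05.

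Under the stated analysis, the trial could report that the device identifies periods of deterioration on the strength of a significant slope, without ever having estimated discrimination. That matters because the integrated arm uses the signals to draw clinicians' attention to change, and the Discussion looks ahead to remote monitoring of severely unwell patients. The randomized comparison is not affected, but one of the two stated aims would not be tested as posed.

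**Working it through.** **The plan's own figure.** For effect size 0.5, 80% power and two-sided α of .05, n per group = 2 × (1.960 + 0.842)² / 0.5² = 62.8, so 63. This reproduces, but it sizes only the comparison between arms. No figure is given for Aim 2.

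**Inputs from the article.** Aim 2 is restricted to the integrated arm (63 participants). CGI and SOFAS are rated monthly over 6 months, so about 6 ratings per participant.

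**Assumptions, because the article gives no figures.** Complete data, independent months within a participant, one device signal and one score, and deterioration in 5%, 10% or 20% of months.

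**Step 1: when is the slope significant?** A model with participant fixed effects leaves 63 × 6 − 63 − 1 = 314 residual df. The critical t is 1.968, so the critical within-person correlation is 1.968 / √(314 + 1.968²) = 0.110. At r = 0.15, t = 0.15 × √(314 / (1 − 0.15²)) = 2.69, P = .0076. The correlation that gives 80% power is about 0.16, that is R² of about 2.5%.

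**Step 2: what discrimination goes with that correlation?** This depends on how the score behaves in stable months, so two cases are set side by side.

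- *Case A, normal scores.* Signal and score are bivariate normal with correlation r, and the worst share p of months counts as deteriorated. The AUC follows numerically from that distribution.
- *Case B, flat scores.* The score changes only in deteriorated months, and the signal is normal with its mean shifted by d standard deviations in those months. Then d = [r / √(1 − r²)] / √(p(1 − p)) and AUC = Φ(d / √2). Example: r = 0.15 and p = 0.10 give d = 0.1517 / 0.30 = 0.506 and AUC = Φ(0.358) = 0.64.

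| r | Months deteriorated | AUC, case A | AUC, case B |
|---|---|---|---|
| 0.15 | 5% | 0.59 | 0.69 |
| 0.15 | 10% | 0.58 | 0.64 |
| 0.15 | 20% | 0.57 | 0.61 |
| 0.30 | 5% | 0.68 | 0.85 |
| 0.30 | 10% | 0.66 | 0.77 |
| 0.30 | 20% | 0.65 | 0.71 |

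In case A at r = 0.15, with specificity set at 80%, sensitivity is 28% to 30% and positive predictive value is 7% (5% deteriorated) to 26% (20% deteriorated).

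**Step 3: reading the table.** The same correlation, with the same P value, goes with an AUC anywhere from 0.57 to 0.69 at r = 0.15, and from 0.65 to 0.85 at r = 0.30. The slope and its P value do not determine how well the two states are separated.

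**Step 4: precision of a direct estimate.** At a 10% rate there are 0.10 × 378 ≈ 38 deteriorated months and 340 others. The Hanley–McNeil formula at AUC 0.60 gives a standard error of about 0.05, so roughly ±0.10 for a 95% interval before any allowance for clustering.

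**The case against.** **The article is a summary.** Cut-offs, accuracy measures and validation are often left to the full protocol or the SAP, and naming a model family does not exclude them. This stands as far as it goes: a reader might infer that no discrimination analysis exists anywhere, and the document cannot show that. The point rests instead on the mismatch between an aim worded as detection and a method stated in firm terms. The RCT paragraph is hedged with *may* and *could*, whereas the within-subjects sentence says what the analysis will consist of.

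**Stable months need not drive the slope.** A reader might infer from the Discussion that the slope would come mainly from small fluctuations in well months. The article says only that patients are more often stable and gives nothing on the size of fluctuations. A participant whose 7-point CGI score never changes adds nothing to a within-person covariance, so if stable months are flat, the deteriorations drive the slope. A constructed simulation in which physiology tracks the score only in stable months (slope 0.2 to 0.3) gave a significant slope in about 75% to 100% of trials with AUC 0.50. That shows what is possible; it is not a feature of this plan.

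**The outcomes are not a single severity score.** The models cover several outcomes, and the CGI has a treatment response scale besides severity. That is correct, but all are still modelled as scores.

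**Discrimination might be good.** A reader might infer that detection will be near chance, or that most alerts will be false. Case B at r = 0.30 reaches an AUC of 0.71 to 0.85, so near-chance detection does not follow. Nor does a false-alert rate: the dashboard relies on visual inspection and speed meters with no numeric threshold given, and the response is left to clinical judgement.

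**Conclusion.** The point holds as a mismatch between Aim 2 and its stated analysis. A significant slope would support association and leave detection unmeasured. A within-person correlation just above 0.11 is enough for significance. At 0.15 the implied AUC is about 0.57 to 0.69 across both cases, which is weak discrimination; at 0.30 it runs from 0.65 to 0.85 and depends on how scores behave in stable months. These figures rest on 63 participants with 6 complete, independent monthly ratings and an assumed 5% to 20% of months deteriorated. The mismatch itself rests on none of them. It should be corrected, but it leaves the primary randomized comparison untouched.

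**What to change.** Keep the linear models and add a pre-specified within-person discrimination analysis in the integrated arm.

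1. **Define a deteriorated period for analysis** from data already planned: blinded CGI worse than the participant's own baseline or stable level, and/or charted relapse or hospitalization. Anchoring on the participant's own level, not on the previous month, means that sustained deterioration still counts.
2. **Model that state** on the device signals with a mixed or conditional logistic model.
3. **Report** AUC, sensitivity, specificity and predictive value, with confidence intervals that allow for clustering by participant and with cross-validation that leaves out whole participants.
4. **Tie the wording to the estimates.** Base any statement that the device detects or identifies deterioration on these estimates and their intervals. If the sponsor prefers the linear models alone, reword Aim 2 and Hypothesis 2 as an association between physiology and scores.

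The cost is analysis text and programming; no new data are needed. The drawback is precision: with about 38 deteriorated months at a 10% rate, the intervals will be wide. For the same reason a fixed pass mark on the lower confidence limit of the AUC is not proposed, since modest discrimination could rarely meet it.

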**Methods:**

This study examines whether physiological information from an mHealth device prevents mental deterioration when shared with the participant and clinical team versus with the participant alone. A randomized controlled trial (RCT) will allocate 126 young adults from community mental health services for 6 months to standard case management combined with an integrated mHealth device (ie, physiological information is viewed by both participant and case manager: unWIRED intervention) or an unintegrated mHealth device (ie, participant alone self-monitors: control). Participants will wear the Empatica Embrace2 device, which continuously records electrodermal activity and actigraphy (ie, rest and activity). The study also examines whether the Embrace2 can detect periods of mental health versus deterioration. A variety of measurements will be taken, including physiological data from the Embrace2; participant and case manager self-report regarding symptoms, functioning, and quality of life; chart reviews; and ecological momentary assessments of stress in real time. Changes in each participant’s Clinical Global Impression Scale scores will be assessed by blinded raters as the primary outcome. In addition, participants and case managers will provide qualitative data regarding their experience with the integrated mHealth device, which will be thematically analyzed.

**Results:**

The study has received ethical approval from the Western Sydney Local Health District Human Research Ethics Committee. It is due to start in October 2020 and conclude in October 2022.

**Conclusions:**

The RCT will provide insight as to whether an integrated mHealth device enables case managers and participants to pre-emptively manage early warning signs and prevent relapse. We anticipate that unWIRED will enhance early intervention by improving detection of stress and allowing case managers and patients to better engage and respond to symptoms.

**Trial Registration:**

Australian New Zealand Clinical Trials Registry (ANZCTR) ACTRN12620000642987; https://www.anzctr.org.au/ACTRN12620000642987.aspx

**International Registered Report Identifier (IRRID):**

PRR1-10.2196/19510

## Introduction

### Overview

Severe mental illnesses, such as schizophrenia, bipolar disorder, and borderline personality disorder are associated with considerable burden and have their peak onset during early adulthood [1,2]. These disorders are highly disruptive in terms of functioning, impairing a young adult’s ability to maintain close relationships, educate themselves, and find employment [1,3]. For example, youths at risk of psychotic illnesses often experience significant functional decline alongside the onset of symptoms [4,5]. The extent to which a mental illness prevents functioning is often the threshold for a psychiatric diagnosis [6,7]. Severe mental illness is also associated with high levels of distress and high rates of suicide compared to the general population [8]. While there is typically no cure for severe mental illness, symptoms can be managed in the community with combinations of medications and/or psychosocial treatments [9,10]. Effective case management requires collaboration between patient and clinician, as well as rapid identification and treatment of early warning signs [3,11]. Yet case management faces several challenges, including patients having limited insight into emerging symptoms and case managers not being able to respond promptly [3,9]. Even small delays prior to intervention could mean the difference between a minor relapse and a lengthy hospitalization.

A potential means to enhance early intervention and engagement is through the use of an inexpensive mobile health (mHealth) device that measures physiological indicators of stress and returns this information to patients and case managers. Across the spectrum of mental disorders, elevated stress levels are known to increase risk of relapse. The body and mind have systems that maintain a homeostatic state and these can be disrupted by acute or chronic stress [12,13]. For example, stress can impact upon the autonomic nervous system and circadian rhythms, causing changes in arousal and sleep patterns, respectively. While small amounts of stress can be beneficial, acute or prolonged stress is harmful, and individuals with mental illness are particularly sensitive to these effects. An mHealth device can be worn like a wristwatch that can reliably and continuously measure physiological signs of stress. For example, mHealth devices can measure arousal through electrodermal activity (EDA). An mHealth device can also measure actigraphy, which is a noninvasive method of monitoring human rest and activity cycles [14]. A small actigraphy unit has an accelerometer that measures gross motor activity across three axes. These measurements can be converted into variables of interest, such as step counts and periods of rest. Changes in these measures may indicate an individual is experiencing a level of stress that could be harmful. For example, a combination of high arousal and poor sleep suggests a stress response associated with greater risk of relapse. Less activity could be associated with a depressive state and greater levels could be associated with a manic state [15]. Physiological data from an mHealth device can also be combined with other related variables to predict relapse [15,16]. For example, an ecological momentary assessment (EMA) [17] involves taking subjective measurements of an individual’s current mental state, which can be used in conjunction with physiological data from an mHealth device.

mHealth devices have been used effectively for managing and monitoring physical conditions such as cardiovascular disorders, diabetes, and obesity [18]. More recently, continuous data from an mHealth device has shown promise in predicting signs of stress and mental deterioration. For example, Sano and colleagues [19] examined whether physiological and behavioral measures collected by wearable sensors and mobile phones could predict stress and poor mental health in a large student sample (N=201). They used machine learning, a subfield of artificial intelligence, to analyze the multimodal data. The mHealth devices classified students into high- or low-stress groups 78.3% of the time and as experiencing high or low mental health 87% of the time. Cella and colleagues [20] used an mHealth device to compare heart rate, EDA, and movement for 30 participants with schizophrenia in the community and 25 controls. Compared to controls, participants with schizophrenia showed lower heart rate variability, movement, and functioning, consistent with autonomic dysregulation. Positive symptoms were also correlated with parasympathetic dysregulation. Most recently, Cella and colleagues [21] asked participants with first episode psychosis to wear an mHealth device to continuously measure their heart rate variability and EDA while self-reporting psychotic symptoms. They found higher EDA during periods where participants were experiencing psychosis.

The use of an mHealth device in younger adults with mental illness over extended periods has yet to be tested. This age group is more likely to be “tech savvy” and they are at high risk of developing severe mental illness. Pilot data indicate 15 out of 19 young adults with severe mental illness wore an mHealth device for greater than two weeks, and information regarding each participant’s activity, sleep, EDA, and subjective stress was reliably collected during this period [22]. The next challenge is establishing if this information is clinically useful and predicts relapse. This protocol describes using information from an mHealth device streamed to both case managers and patients to allow them to independently monitor and then collaborate to manage any early warning signs (see Figure 1).

